### Primary outcomes

The primary outcome is the proportion of participants who achieve treatment success defined as seizure freedom while taking the prescribed ASM for the duration of the 12-month follow-up period. This outcome is consistent with the ILAE and European Medicines Agency guidelines for ASM monotherapy trials.^20^ This outcome is also clinically relevant given that seizure freedom is associated with improvement in quality of life in people with epilepsy.^2^

### Secondary outcomes

Treatment failure is defined as withdrawal of the initial ASM or the commencement of polytherapy with a second ASM, whichever is earliest.Time to first seizure after treatment initiation.Direct healthcare costs will be assessed through review of a participant managed diary at both 28 weeks and 52-week post-treatment collection.Indirect healthcare costs will be assessed as a measure of productivity loss determined from the Work Productivity and Activity Impairment–General Health questionnaire, collected at baseline, 28 weeks and 52 weeks post-treatment commencement.The incidence of depression and anxiety will be assessed through changes to HADS scores^21^ over the treatment period, which will be collected at baseline, 28 weeks and 52 weeks post-treatment commencement.Comparison of the proportion of participants who achieve a minimum increase of 12 points in the Quality of Life in Epilepsy-31 (QOLIE-31) as a measure of quality of life,^22^ supported by the general European Quality of Life-5 Dimensions-5 Level (EQ-5D-5L) survey,^23^ both of which are collected at baseline, 28 weeks and 52 weeks post-treatment commencement.To assess clinical and participant acceptance of using ML to select the first ASM, participants and neurologists involved in the trial will be invited to take part in an optional process evaluation, involving:A study-specific questionnaire developed based on the Unified Theory of Acceptance and Use of Technology 2.^24^Qualitative interviews of 25% of study patients and 25% of study neurologists.

### Economic evaluation

Within-trial analysis of cost-effectiveness will compare differences in combined direct and indirect costs between the ML and usual care against differences for both quality-adjusted life-years and the 1-year seizure freedom rate. To ensure real-world relevance, prospective trial data will be analysed using the utility score indices from the EQ-5D-5L and QOLIE-31 overall score. This approach has been used in a previous health economic evaluation in epilepsy.^25^ If the results from this analysis indicate an increase in the seizure-free rate and quality of life, or a reduction in costs, extrapolation-based analysis over an extended time-horizon will be performed where costs and effects are expected to be discounted by the standard Australian 5% annual rate.

### Statistical analysis

Analysis of efficacy will be done for the intention-to-treat (ITT) set (all randomised patients who have taken at least one dose of the prescribed ASM) and the per-protocol set (patients in the ML group for whom neurologists did not prescribe the recommended drug will be excluded). The Cochran-Mantel-Haenszel test stratified by centres (to account for variation between centres) will compare the differences in 12-month seizure-free rate; retention rate (affected by both efficacy and tolerability) of the initial treatment at 1 year; and proportion of patients who achieve clinically meaningful improvement in quality of life. Cox regression will be used to assess differences in time to treatment failure and time to first seizure after treatment initiation between the two groups. Prescription patterns of the two groups will be compared. In the ML group, we will also compare the outcomes between patients who are prescribed the ML recommended ASMs and those who are prescribed non-ML recommended ASMs by their neurologists. This will include analysis of the reason provided by the neurologists in cases where ML recommendation was rejected. Also, the outcomes of different ASM groups such as sodium channel blockers versus non-sodium channel blockers will be compared.

Validation of EpiMD in the control group will be done by comparing the predicted response to the neurologist-selected ASM treatment outcome. A probability threshold of 0.55 will be applied in classifying treatment success or failure to calculate the model’s sensitivity, specificity and area under the curve.

To assess cost-effectiveness in the economic evaluation, cost differences and effect differences for 10 000 bootstrap draws will be analysed from the trial dataset over a 1-year time horizon. This will be represented using a cost-effective plane and a cost-effectiveness acceptability curve.^26^ This analysis will be performed both from the public healthcare and societal perspective. Consideration was given to the inclusion of an elderly cohort, particularly due to the prevalence of epilepsy in this age group. However, to match the current retirement age, we intend to maintain the upper age limit of 67. Based on the analytic results, future study directions such as extended follow-up duration will be considered, and given the distinct health and social needs of the older adult population,^27^ we propose the future development of a model specific to this cohort.

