### Randomisation and ASM prescription

The participant will be randomised 1:1 into either the experimental (ML group) or the control group (usual care group) using individual randomisation centralised and in blocks that are stratified by both seizure type (focal vs generalised onset) and study site. In the experimental group, EpiMD will be run using the information provided and respond with the ASM recommendation. The investigator will prescribe the recommended ASM unless it is considered to be contraindicated due to safety reasons. In this case, the investigator will prescribe a different ASM and provide their reasoning for doing so. In the control group, the recommendation by the ML model will not be revealed, and the investigator will prescribe an ASM based only on their clinical judgement.

Any out-of-pocket costs associated with new generation ASMs used as monotherapy that are not covered by the Pharmaceutical Benefits Scheme will be reimbursed to the participants. ASM prescription will be open label for both groups. Guidance regarding the rate of titration, initial maintenance dose and any subsequent increments or decrements will be made available to the prescribing clinician. If the patient is taking an ASM prior to randomisation, the drug will be ceased over 2–4 weeks under the supervision of the treating neurologist.

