### Blinding

Both the participant receiving treatment and the neurologist assessing outcomes at follow-up visits will be blinded as to which group the participant has been assigned; however, neither the patient nor the treating neurologist will be blinded to the ASM that is being taken. Blinding will be maintained through either of two methods. In method 1, the referring neurologist will act as the investigator at the baseline visit and prescribe the ASM, and different neurologist(s) will perform all subsequent follow-up. In method 2, a neurologist different from the referring one will prescribe the ASM at the baseline visit, and the referring neurologist will perform all subsequent follow-up. This allows the continuity of care at participating epilepsy clinics to be maintained.

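### The set labelled intention-to-treat requires at least one dose, so it is a modified ITT set, and no analysis of all randomised participants is named

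*Protocol article*

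**What the plan says.** The Statistical analysis section names two efficacy sets. The first is the "intention-to-treat (ITT) set (all randomised patients who have taken at least one dose of the prescribed ASM". The second is "the per-protocol set (patients in the ML group for whom neurologists did not prescribe the recommended drug will be excluded". Neither contains every randomised participant. The Sample size section labels its hypothesised effect, 55% against 35%, as an ITT effect, so the first set carries the primary claim.

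On the order of events, Randomisation and ASM prescription says that "The participant will be randomised 1:1 into either the experimental (ML group) or the control group (usual care group" takes place first. Drug choice follows: "In the experimental group, EpiMD will be run using the information provided and respond with the ASM recommendation", whereas in usual care the investigator chooses without seeing the model's output. The same section says "ASM prescription will be open label for both groups". The Blinding section masks the participant to group, but adds that "neither the patient nor the treating neurologist will be blinded to the ASM that is being taken".

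Primary outcomes defines "treatment success defined as seizure freedom while taking the prescribed ASM for the duration of the 12-month follow-up period".

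**The concern.** A one-dose rule is usually tolerated when masking makes the decision to start independent of the arm. That protection is weak here. Group assignment acts through the drug that is chosen, and the participant knows the drug before deciding whether to take it. Whether a first dose is taken is thus a post-randomisation event that assignment can influence.

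The trial asks whether one selection strategy leads to more treatment successes than another. A selected drug that the participant never starts is an unsuccessful outcome of the strategy, and the one-dose rule removes it from the denominator. The arm with more such outcomes then looks better than it was. The result would also be reported as ITT when it is not, with no all-randomised analysis beside it to show the difference.

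**Working it through.** **1. The plan's own figure.** Inputs from Sample size: 35% against 55%, one-sided 0.025, 80% power, 10% investigator non-compliance, 10% dropout, 95th percentile of 1000 simulations. With the unpooled normal approximation, n per group = (1.960 + 0.842)² × (0.35×0.65 + 0.55×0.45) / 0.20² = 93.2, so 94. Drawing the control rate from Binomial(1000, 0.35) with a fixed 20-point gain, the 95th percentile is also 94. Then 94 / (0.9 × 0.9) = 116.05, so 117 per group and 234 in total. The stated size reproduces and is not in dispute.

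**2. Is the outcome of a never-starter known?** Success requires freedom from seizures while on the prescribed drug over the whole 12 months. Someone who never takes it cannot meet that, so the result is a non-success and nothing has to be imputed. Missing outcome data are no reason for the exclusion.

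**3. Bias under the null.** Let d be the share in an arm who never start. With 35% success among all randomised in both arms, and never-starters counted as non-successes, the dosed-only rate is 0.35 / (1 − d). The spurious difference is

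0.35 / (1 − d_ML) − 0.35 / (1 − d_UC).

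The article gives no value for d, so 0% to 10% is assumed. Type I error is for an unstratified pooled z-test, as an approximation to the planned Cochran-Mantel-Haenszel test, with 117 randomised per arm.

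| Never start, ML / usual care | Dosed-only rates | Spurious difference (points) | One-sided type I error (nominal 0.025) |
|---|---|---|---|
| 5% / 5% | 36.8% / 36.8% | 0.0 | 0.025 |
| 5% / 2% | 36.8% / 35.7% | +1.1 | 0.037 |
| 5% / 1% | 36.8% / 35.4% | +1.5 | 0.042 |
| 5% / 0% | 36.8% / 35.0% | +1.8 | 0.048 |
| 10% / 2% | 38.9% / 35.7% | +3.2 | 0.070 |
| 0% / 5% | 35.0% / 36.8% | −1.8 | 0.012 |

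**4. How few participants matter in a close result.** Suppose 55/117 successes against 41/117: difference 12.0 points, pooled standard error 6.43 points, z = 1.86, one-sided p = 0.031. If three of the ML participants never took a dose, the protocol's set gives 55/114 against 41/117: 13.2 points, z = 2.04, p = 0.021, which crosses 0.025. If the three were in usual care instead, 55/117 against 41/114 gives p = 0.044. These counts were chosen close to the threshold.

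**5. Effect of the remedy on power.** Suppose success among those dosed is 55% against 35%. The all-randomised difference is 0.55(1 − d_ML) − 0.35(1 − d_UC). Power is for 117 analysed per arm, with no dropout deducted.

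| Never start, ML / usual care | All-randomised difference (points) | Power, all randomised | Power, dosed only |
|---|---|---|---|
| 5% / 5% | 19.0 | 84% | 86% |
| 5% / 0% | 17.3 | 76% | 86% |
| 10% / 0% | 14.5 | 61% | 85% |
| 0% / 5% | 21.8 | 92% | 86% |

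**The case against.** The strongest reply is that differential never-starting may be rare. Participants do not know their group, so distrust of a computer's recommendation cannot by itself drive refusal. An investigator prescribes in both arms, the choice is confined to seven commonly used drugs, and out-of-pocket costs are reimbursed. At 117 per arm the standard error of the difference is √(2 × 0.35 × 0.65 / 117) = 6.2 points. A 1.5-point bias is about a quarter of that and a 3.2-point bias about half, and the latter needs roughly 12 never-starters against 2. All of this stands as a limit on size. It does not rescue the definition, because reluctance about a named drug remains possible and the mix of drugs is what differs between the arms.

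Three stronger readings are tempting, and the article supports none of them.

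- A reader might infer that the rule favours the ML arm. No never-start rate is given for either arm, and the reverse imbalance makes the test conservative.
- A reader might say that participants are excluded because of the drug they were allocated. They are allocated a selection strategy, and the drug follows from it.
- A reader might assume that anyone re-prescribed before a first dose is excluded. The set refers to the prescribed drug without saying whether that means the first one prescribed, so the text does not settle this.

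Nor can the matter be left to an unseen analysis plan: the article states the definition, and the definition does not fit its label.

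**Conclusion.** The point holds as one about the definition and label of the primary analysis set. The set called ITT is a modified ITT set, no all-randomised efficacy analysis is named, and the exclusion rests on a post-randomisation event that can differ by arm. It is also unnecessary, since the primary outcome already classifies a never-starter.

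Size and direction are unknown. Under the assumed never-start rates and 35% success in both arms, the spurious difference runs from −1.8 to +3.2 points against a planned effect of 20, with one-sided type I error from 0.012 to 0.070. Equal rates give no bias under the null. The bias is small if never-starters are few or balanced, and could decide a close result if they are not. A reader might take this as showing that the trial will be biased or that its sample size is wrong; the article supports neither conclusion.

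**What to change.** Define the ITT set as all randomised participants, analysed in the group to which they were assigned. State that those who never start the prescribed drug count as not achieving treatment success, in line with the primary outcome. Keep the at-least-one-dose set as a sensitivity analysis labelled modified ITT. Say how participants re-prescribed before a first dose are handled, and report the number of never-starters by arm. Make the change before group-level results are seen.

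The wording is cheap to change, but the change has a price. Success rates will be lower than in the dosed-only set. If success among those dosed is 55% against 35%, power falls to about 84% at 5%/5% never-starting and 76% at 5%/0%, against about 85–86% in the dosed-only set. That possible loss should be disclosed. The recruited 234 need not change.

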### Sample size

Based on previous RCTs in newly diagnosed epilepsy^29^,^32^ and observation in the Glasgow and Perth cohorts,^4 33^ the 12-month seizure-free rate on the first ASM in the usual care group is assumed to be 35% and to follow a distribution of Binomial (1000, 0.35) in participating sites. In keeping with ILAE recommendations for detecting clinically significant benefit,^34^ we hypothesise that the ITT 12-month seizure rate will be 20% higher (ie, 55%) when EpiMD is used. Allowing for non-compliance with the recommended drug by the investigators in 10% of patients in the ML group, with a one-sided significance level of 0.025 and 80% power, accounting for 10% dropout, a total of 234 participants (117 patients per group) will be recruited, determined from the 95th percentile of 1000 simulations. This will provide 90% power to detect a 23% higher ITT 1-year seizure rate in the ML group. This sample size will provide 80% power for the same minimal detectable effect size in retention rates and proportion of patients who report clinically meaningful improvement in QOLIE-31 total score. Additionally, this will provide for a minimum detectable HR of 0.58 in exit due to lack of efficacy, adverse events or any reason, and time to first seizure, assuming overall at least 50% event rates.

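### The per-protocol set drops overridden patients from the ML arm only, so this second efficacy comparison is not randomised and may be biased in either direction

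*Protocol article*

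**What the plan says.** Under Statistical analysis, the protocol article sets out two efficacy populations. The ITT set is "all randomised patients who have taken at least one dose of the prescribed ASM". The per-protocol set is defined by one rule: "patients in the ML group for whom neurologists did not prescribe the recommended drug will be excluded". No exclusion is stated for usual care, and the section does not rank the two sets.

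Under Randomisation and ASM prescription, the ground for an override is given: "The investigator will prescribe the recommended ASM unless it is considered to be contraindicated due to safety reasons". In that case the investigator chooses another drug and records the reason. For usual care, "In the control group, the recommendation by the ML model will not be revealed".

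Under Sample size, the effect is hypothesised on the ITT rate, "Allowing for non-compliance with the recommended drug by the investigators in 10% of patients in the ML group". The Statistical analysis section also plans, within the ML group, to "compare the outcomes between patients who are prescribed the ML recommended ASMs and those who are prescribed non-ML recommended ASMs by their neurologists".

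**The concern.** The exclusion depends on something that happens after allocation and can happen in one arm only. The investigator sees the recommendation, judges it unsafe for that patient, and the patient leaves the per-protocol set. Patients with the same features in usual care have no recommendation to override, so all of them remain. A selected part of the ML arm is then compared with the whole control arm. If overridden patients have a different chance of success from the rest, the arms differ even when EpiMD does nothing.

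The result would naturally be read as the effect when the recommendation is followed, and the design does not deliver that. The comparison of accepted with overridden patients inside the ML arm has the same selection problem and few patients on one side.

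**Working it through.** **Inputs from the article.** The override share is f = 10%. The sample-size section says "the 12-month seizure-free rate on the first ASM in the usual care group is assumed to be 35"%, with 55% hypothesised in the ML arm. The test is one-sided at 0.025 with 80% power and 10% dropout, and 117 patients are randomised per group.

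**Assumption.** The success rate s among overridden patients is not documented, so it is shown as a range.

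**The plan's own figure.** The usual two-proportion formula gives [1.960·√(2·0.45·0.55) + 0.842·√(0.35·0.65 + 0.55·0.45)]² / 0.20² = 96 per arm, or 106 with continuity correction. Then 106/0.90 = 118 per arm, 236 in all, against 234 stated. The match depends on the continuity correction, and the article's simulation step is not described fully enough to rerun. The sample size is not disputed here. After dropout, 117 × 0.90 ≈ 105 per arm.

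**Bias with no true effect.** Success is 35% in both arms overall. The ML per-protocol rate is (0.35 - f·s)/(1 - f), so the bias is f/(1 - f) × (0.35 - s). At f = 10% the multiplier is 0.10/0.90 = 0.111. The last column is the chance that a one-sided 0.025 pooled z-test declares benefit, by normal approximation, with 105 per arm before exclusion.

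| s (assumed) | ML per-protocol rate | Bias (points) | Chance of declaring benefit |
|---|---|---|---|
| 0% (extreme) | 0.350/0.90 = 38.9% | +3.9 | 8.2% |
| 20% | 0.330/0.90 = 36.7% | +1.7 | 4.3% |
| 35% | 0.315/0.90 = 35.0% | 0 | 2.5% |
| 45% | 0.305/0.90 = 33.9% | -1.1 | 1.7% |

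Seeded simulations (400,000 trials per scenario) gave 8.3% and 4.4% for the first two rows. In every simulated scenario the ITT test stayed at about 2.5 to 2.6%. When the same would-be-overridden patients were removed from both arms, the rejection rate was also 2.5 to 2.6%, so the one-sidedness of the exclusion causes the excess.

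**Bias under the planned effect.** Suppose the ML arm reaches 55% overall and patients of the overridden kind succeed at 20% in either arm. The per-protocol contrast is (0.55 - 0.02)/0.90 - 0.35 = 58.9% - 35.0% = 23.9 points. Among patients in whom the advice would be followed, the true contrast is 58.9% - 36.7% = 22.2 points. The excess is again 1.7 points.

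**Complier-average effect.** The ITT difference divided by the share of the ML arm that followed the advice is 0.20/0.90 = 22.2 points. It is zero when the ITT difference is zero, whatever s is.

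**Why the exposure must be worded carefully.** This divisor holds only if the exposure is zero in controls. Some controls will happen to receive the drug that EpiMD ranks first. If receipt of that drug were the exposure, the divisor would be the ML share minus the control share. With assumed control shares of 1/7 and 30%, the 20-point difference becomes 0.20/(0.90 - 0.143) = 26.4 points and 0.20/(0.90 - 0.30) = 33.3 points.

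**Within-ML comparison.** 10% of 117 is 11.7, so about 12 overridden patients.

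**The case against.** The strongest reply is that the trial's conclusion does not rest on this set. The hypothesis and the power for seizure freedom are stated on the ITT rate, ITT is named first, and a per-protocol analysis is normally supportive. How the two are ranked may be settled in an analysis plan that is not shown. All of that stands. A reader might infer that the main efficacy result is biased; the documents do not support that, since the ITT set keeps overridden patients in their allocated arm.

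A reader might also infer that the exclusion flatters EpiMD. That requires overridden patients to do worse, and nothing in the article links a drug-specific contraindication to a lower chance of seizure freedom. Several serious conditions are already ineligible, and valproate is filtered out for women aged 18 to 45. Equal prognosis gives no bias, and better prognosis gives bias against EpiMD.

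Larger figures are possible with more overrides: at an assumed 20% with s = 20%, 0.20/0.80 × 0.15 = 3.75 points. But 10% is the only documented rate, and there even the extreme case is small beside the 20-point target.

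The replacement is not assumption-free either. An investigator who overrides has seen the recommendation and must justify departing from it, so the substitute drug need not be the one usual care would have given. That also stands and must be stated. Finally, the article names no test for accepted versus overridden patients, so that part needs only a clarification.

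None of this repairs the rule as written. The exclusion is one-sided, its bias cannot be signed in advance, and recruiting more patients does not remove it.

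**Conclusion.** The concern holds for the per-protocol comparison and for nothing beyond it. At the documented 10% override rate, the bias under no effect runs from +3.9 points in the extreme case through zero to -1.1 points if overridden patients succeed at 45%; a higher success rate would take it further below zero. The false-positive rate of that comparison moves from 2.5% to 4.3% at s = 20%, to 8.2% at the extreme, and down to 1.7% at s = 45%.

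These sizes rest on the article's 35% and 10%, on about 105 analysed per arm, and on assumed values of s. The documents support saying that a spurious benefit is possible, not that it is expected. The change is worth making because the rule is fixed in the text and an estimate that respects randomisation is available at little cost.

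**What to change.** Keep ITT as the main analysis and replace the one-sided per-protocol comparison with a complier-average causal effect:

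- **Instrument:** randomised allocation.
- **Exposure:** a revealed EpiMD recommendation was followed. This is zero in usual care by design, because nothing is revealed there.
- **Estimate:** the ITT difference divided by the proportion of the ML arm in whom the recommendation was followed, with the stratification already planned and a confidence interval.
- **If the exposure is instead receipt of the drug that EpiMD ranks first:** use as divisor the ML proportion minus the control proportion receiving it. This needs the model's ranking for controls. The article already plans model predictions in that arm: "Validation of EpiMD in the control group will be done by comparing the predicted response to the neurologist-selected ASM treatment outcome".
- **Assumption to state:** an override made after seeing the recommendation leads to the same outcome that usual care would have given that patient.
- **Accepted versus overridden ML patients:** report as descriptive only, with the override reasons.

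The cost is a wording change, best made before unblinding, and a small amount of analysis. Treating the followed share as known, the interval is 1/0.90 = 1.11 times as wide as the ITT interval, and the stated assumption cannot be tested in the trial.

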**Figure 1 F1:**
[figure not shown]
Study recruitment pathway. Study recruitment pathway showing sequencing of referral, screening and consenting procedures, in addition to randomisation into the two study groups, before merging into an identical follow-up pathway. ASM, antiseizure medication; ML, machine learning; UC, usual care.

At the baseline visit, if all the eligibility criteria are fulfilled, the PICF will be signed by the participant and investigator. The baseline questionnaires will be completed by the participant, guided by the neurologist and study coordinator, to collect clinical variables alongside diagnostic test reports from the patient electronic medical record (EMR). Additionally, the content and utilisation of both the seizure diary and the healthcare use diary that will be completed at follow-up visits will be explained to the participant. Study data are collected and managed using Research Electronic Data Capture (REDCap) tool hosted and managed by Helix (Monash University).^15 16^ REDCap is a secure, web-based software platform designed to support data capture for research studies. It provides an intuitive interface for validated data capture and audit trails for tracking data manipulation and export procedures. REDCap will be used to automate the export procedures for data downloads to common statistical packages and the procedures for data integration and interoperability with external sources. The trial REDCap is updated anytime the model is utilised, and therefore, is suitable to meet our obligations regarding data management and site monitoring.

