#### ML model

The code required to run EpiMD is hosted on a secure Australian Research Data Commons Nectar Research Cloud instance using Monash University access. Once all clinical variables required for the model have been entered in the REDCap survey, the investigator can follow a secure REDCap link that will initiate a run of the model and direct them back to the study REDCap where the model results can be found. After the processing time has completed, the recommendation will be sent to the REDCap result page. This page will display the results of the model and contain a text field to provide feedback about the decision-making surrounding the ASM recommendation (ie, whether the clinician chooses to prescribe the recommended ASM). This feedback, along with the individual score for each ASM assessed, will be retained for later analysis. For quality control and troubleshooting, an activity log of all variables and results that have been sent to and from the model is maintained on the model server.

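### The primary test is valid but uses no patient-level baseline predictor, although one can be computed in both arms from data already collected; the power at stake is modest and conditional

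*Protocol article*

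**What the plan says.** The Statistical analysis section of the protocol article names the test for the primary outcome: "The Cochran-Mantel-Haenszel test stratified by centres (to account for variation between centres) will compare the differences in 12-month seizure-free rate". It describes no covariate-adjusted analysis of seizure freedom. Randomisation is "stratified by both seizure type (focal vs generalised onset) and study site" (Randomisation and ASM prescription), so seizure type, a randomisation factor, is also outside the test.

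The article shows that prognostic information is at hand:

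- At the baseline visit, "The baseline questionnaires will be completed by the participant, guided by the neurologist and study coordinator, to collect clinical variables" (Recruitment procedures), together with diagnostic test reports.
- The Introduction says the model was trained to predict 12-month seizure freedom without intolerable adverse effects on each of seven drugs. That is close to the primary outcome.
- The ML model section says of the investigator's comments and the drug scores: "This feedback, along with the individual score for each ASM assessed, will be retained for later analysis".
- Predictions for controls are already needed: "Validation of EpiMD in the control group will be done by comparing the predicted response to the neurologist-selected ASM treatment outcome" (Statistical analysis).

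The plan uses these scores to validate the model but not in the comparison of the arms.

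**The concern.** A stratified Cochran-Mantel-Haenszel test cannot take a continuous covariate. Where a baseline variable predicts the outcome, adjusting for it removes variance that the unadjusted comparison carries, and it deals with chance prognostic imbalance between two groups of 117 by a rule fixed in advance. A summary of the seven EpiMD scores that depends only on baseline inputs is independent of arm by randomisation. Adjusting for it therefore leaves the treatment effect intact, whether or not EpiMD predicts well.

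What is at stake is efficiency in a trial sized at 80% power for a large effect. Neither bias nor a wrong sample size is in question.

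**Working it through.** **1. The plan's own figure.** Inputs from Sample size: 35% v 55%, one-sided 0.025, 80% power, 10% dropout, 234 in total.

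- Uncorrected: n = [1.96·√(2·0.45·0.55) + 0.842·√(0.35·0.65 + 0.55·0.45)]² / 0.20² = 95.9, so 96 per arm.
- With continuity correction: n' = (n/4)·[1 + √(1 + 4/(0.20·n))]² = 105.7, so 106 per arm.
- Dropout: 106/0.9 gives 118 per arm (236 in total), and 106 × 1.1 gives 117 per arm (234 in total).

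The stated 234 reproduces. The claim of 90% power for a 23-point gain also needs 106 per arm with the correction, so it reproduces too.

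**2. Starting power.** Evaluable patients per arm: 117 × 0.9 = 105. The uncorrected normal approximation gives 83.5% power at 35% v 55%.

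**3. Idealised gain.** A covariate explaining a share R² of the outcome variance acts like n = 105/(1 − R²) per arm:

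| R² (assumed) | effective n per arm | power |
|---|---|---|
| 0 | 105.0 | 83.5% |
| 0.03 | 108.2 | 84.6% |
| 0.05 | 110.5 | 85.3% |
| 0.10 | 116.7 | 87.2% |
| 0.18 | 128.0 | 90.0% |

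**4. Simulation of a small model.** 210 evaluable, 14 equal centres of 15, 35% v 55%, 3000 runs per row. Cochran-Mantel-Haenszel by centre was compared with a risk difference adjusted for one score and centre, with a robust standard error:

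| AUC of score (assumed) | CMH | adjusted | gain (points) |
|---|---|---|---|
| 0.50 | 82.2% | 82.4% | 0.2 |
| 0.60 | 84.1% | 85.1% | 1.0 |
| 0.65 | 83.7% | 86.2% | 2.5 |
| 0.70 | 83.9% | 88.0% | 4.1 |
| 0.75 | 84.4% | 90.7% | 6.3 |

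Each power has a simulation error of about √(0.84·0.16/3000) = 0.7 points. One-sided type I error was 2.4% to 2.9% for both methods. This is a favourable case: equal centres and few nuisance terms.

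**5. Simulation of the fuller model.** 210 patients, 14 unequal centres with the small ones pooled, and a risk difference with HC3 robust standard error. The strength of the score is a log-odds slope per SD. For a standard normal score and a 35% control rate, slopes of 0.4, 0.6, 0.8 and 1.0 correspond to AUCs of about 0.61, 0.66, 0.70 and 0.74 (numerical integration of the logistic model).

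| slope per SD | AUC, about | change in power against CMH (points) |
|---|---|---|
| 0 | 0.50 | about −2 |
| 0.4 to 0.6 | 0.61 to 0.66 | 0 to +1 |
| 0.8 | 0.70 | +2.6 |
| 1.0 | 0.74 | +5.5 |

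One-sided type I error stayed between 0.019 and 0.027.

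**6. Why the test must be named.** In a further simulation of 5000 null runs, with unequal centres of 2 to 45 patients kept as unpooled fixed effects, a likelihood-ratio test from the full logistic model had one-sided error of 0.031 to 0.034, against 0.025 to 0.028 for Cochran-Mantel-Haenszel. With a useless score it still showed 85.4% power against 83.4%. Part of such an apparent gain is anticonservatism.

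**The case against.** The strongest reply is that nothing here is an error. Cochran-Mantel-Haenszel by centre is a valid and common primary test, the stated power is met, and a condensed article may leave adjusted analyses to an analysis plan that is not shown. The first two points stand. The third stands only in part, because the article itself fixes the primary test and its sole stratifier.

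The size is also open to challenge, and this stands. No AUC is reported, and even a known AUC for EpiMD would not be that of a mean over seven drugs, since averaging removes the drug-specific part. The adjusted model carries more terms than a score alone, which lowers the gain.

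The seizure count is uncertain as well. Table 1 marks the seizure diary at baseline, while Recruitment procedures describes it as filled in at follow-up visits. Eligibility criteria set seizure thresholds but do not show that a count is recorded, and seizure history may already be among EpiMD's inputs, which are not listed.

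Finally, EpiMD is the intervention. Putting its output into the primary model makes the headline result rely on that software's own score. This is a fair reason for caution, and the retained centre-stratified test answers it.

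A reader might infer that the trial is underpowered or its primary test wrong. The documents do not support that: 234 reproduces, and 55% is stated as the intention-to-treat rate ("we hypothesise that the ITT 12-month seizure rate will be 20% higher (ie, 55%) when EpiMD is used"). A reader might also infer that adjustment costs nothing. With a useless covariate, the full model loses about 2 points.

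**Conclusion.** The point holds as a worthwhile improvement in efficiency. The planned test is valid and misses no stated figure, but it leaves unused baseline information that can be had in both arms without new data. With the full model, the expected gain is about 0 to 3 points of power for a covariate of AUC about 0.60 to 0.70 and about 5 points near 0.75, against a loss of up to about 2 points if it predicts nothing.

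These figures rest on an assumed strength of the covariate, on 35% v 55% with 210 evaluable patients, and on an assumed spread of centre sizes. Gains of 5 to 10 points across the plausible range, which simpler models might suggest, are not supported.

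**What to change.** Before unblinding, prespecify as the primary analysis a covariate-adjusted standardised (marginal) risk difference for 12-month seizure freedom, tested with a named robust standard error, so that the 20-point effect keeps its meaning. A conditional odds ratio would target a different quantity. Adjust for:

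- seizure type and site, with a stated rule for pooling small sites;
- one arm-independent prognostic covariate, for example the mean EpiMD probability over the seven drugs, computed by the same rule from the baseline inputs of every participant in both arms. The score of the drug actually prescribed must never be used, because allocation affects it and adjusting for it would remove part of the effect under test;
- pre-treatment seizure count, only if it is recorded at baseline. Table 1 and Recruitment procedures should be reconciled on this.

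Keep Cochran-Mantel-Haenszel by centre as a sensitivity analysis.

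The cost is wording in the analysis plan and a run of EpiMD on control-group inputs, which the planned validation needs anyway. No patients, visits or data items are added. The downsides are a few extra model parameters, the possible small loss of power given above, and reliance on the software's baseline score in the primary model.
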